## Abstract

**Background:**

Temperament-Based Therapy with Support (TBT-S) is a neurobiologically informed, skills-based intervention for eating disorders in which individuals with anorexia nervosa (AN) and their supports participate together in a multi-family group format over five consecutive days. The program is delivered as an adjunct to treatment as usual (TAU). Although prior studies have demonstrated the feasibility, acceptability, and promising outcomes of TBT-S, its effectiveness remains uncertain, as no previous studies have included a control group. This study aims to evaluate the effectiveness of TBT-S by determining whether adding TBT-S to TAU is superior to TAU alone.

**Methods:**

In this multicenter randomized controlled trial (RCT), 120 adults with a diagnosis of AN or atypical AN (AAN) will be randomized to receive either TBT-S in addition to TAU or TAU alone. Individuals with AN/AAN and their supports will complete assessments before and after the TBT-S treatment week, and at 3- and 12-month follow-ups. The primary outcome is change in eating disorder symptomatology from baseline to the 3-month follow-up. Secondary outcomes include changes in quality of life, psychological health, body mass index (BMI), and health care utilization, as well as changes in quality of life and caregiving experience among supports.

**Discussion:**

If TBT-S is found to be effective in reducing eating disorder psychopathology, it may represent a valuable and scalable adjunct to standard treatment for adults with AN/AAN.

## Introduction

Anorexia nervosa (AN) is a psychiatric disorder associated with substantial functional impairment. It is characterized by restriction of energy intake leading to significantly low body weight, an intense fear of gaining weight or persistent behaviors that interfere with weight gain, and a disturbance in the experience of body weight or shape; associated features may include preoccupation with food, repetitive body checking, compulsive exercise, and marked anxiety related to eating (American Psychiatric Association, 2022). The mortality rate for individuals with AN is significantly greater than for other psychiatric in-patients and for the general population (Miskovic-Wheatley et al., 2023; Walker et al., 2015).

Because of its early age of onset, chronicity and level of disability, AN is responsible for an inordinate burden upon the health services (Wentz, 2023). Chronic courses of AN are common and typically involve severe long-term consequences with several admissions and readmissions to hospital (Muratore and Attia, 2021). For adolescents, family-based treatment has been shown to be associated with high rates of remission and recovery (Monteleone et al., 2022) and is recommended as the first-line treatment approach (NICE, National Institute for Health and Care Excellence, 2020). For adults, there is growing evidence pointing to the usefulness of behaviorally focused psychotherapies, and commonly utilized approaches include Cognitive Behavior Therapy-Enhanced (CBT-E), Specialist Supportive Clinical Management (SSCM), and Maudsley Anorexia Nervosa Treatment for Adults (MANTRA) (Russell et al., 2023). However, there are currently no specific treatment approaches which show clear superiority in the treatment of adults with AN (Costandache et al., 2023). Adults with AN have often had a longer duration of illness, have higher relapse rates and are less responsive to treatment (Costandache et al., 2023; Solmi et al., 2024). Hence, it has been stated that “additional studies in this population are crucial, especially if they might target mechanisms underlying AN or identify core treatment components that help individuals make optimal improvements” (Muratore and Attia, 2021, p. 91).

Temperament based therapy with support (TBT-S) is a neurobiologically-informed skills-based intervention for AN where individuals with AN and their supports (e.g., parent(s), partner, other family member and/or friend) participate together in a multi-family format (Hill et al., 2022). TBT-S directly targets eating disorders symptoms by providing a framework for understanding these behaviors and how to manage them. This framework builds on research from cognitive neuroscience showing that individuals with AN often exhibit heightened cognitive control and rigidity, reduced sensitivity to reward (particularly food-related reward), and altered insula and striatal functioning, which is believed to contribute to persistent eating disorder behaviors, despite negative physiological and psychological consequences (Wierenga et al., 2018; Kaye et al., 2015). It integrates neurobiological psychoeducation and structured skills training to enhance symptom management through a strength-based framework. Rather than pathologizing temperament traits commonly associated with AN, TBT-S leverages these characteristics as adaptive assets in the recovery process and allows for an individually tailored treatment approach—based on a manualized framework (Hill et al., 2022). The TBT-S tools are designed to be action-oriented and trait-aligned, so clients can select tools that build on their specific strengths and help reroute from ED symptom cycles. For example, the “Stop, Reboot, Reroute” tool is a step-by-step method for interrupting eating disorder thoughts/behaviors and choosing a more adaptive action. The TBT-S toolbox draws from other eating disorder treatment approaches and is intended as a selection of strategies which could be helpful for managing symptoms while aligning with the individual’s temperament traits. Because supports learn the same tools, they can use these to help coach during meals, distress, and high-risk moments. Building on research showing that family therapy—and possibly in particular multifamily therapy—is helpful in treating individuals with AN (Wierenga et al., 2018), supports are included and have an active role throughout the treatment week. This can aid in reducing isolation and increases accountability—as well as helping to translate TBT-S tools into daily life and thereby sustain treatment gains over time.

TBT-S is an intensive treatment delivered over five consecutive days for a total of approximately 35-40 hours - as an adjunct to treatment as usual (TAU) (Wierenga et al., 2018). It has demonstrated good feasibility, acceptability and outcomes in uncontrolled trials (Wierenga et al., 2018; Knatz Peck et al., 2021; Stedal et al., 2023; Skoog et al., 2025). After TBT-S, 31% of adults with AN were fully or partially remitted, and at 6 months follow-up, 61% of the participants were considered partially or fully remitted (Wierenga et al., 2018). Similarly, for young-adults, full or partial remissions were reported for 39% post TBT-S treatment, and for 56% at 1 year follow-up (Knatz Peck et al., 2021). Studies have also demonstrated improvements in eating disorder psychopathology and clinical impairment, both immediately after receiving TBT-S (Stedal et al., 2023) and at six (Wierenga et al., 2018) and 12 month (Knatz Peck et al., 2021; Skoog et al., 2025) follow-ups. However, these previous studies are limited by a lack of control group. Thus, there is a need for fully powered randomized controlled trials (RCTs) with longer follow-up periods to further establish the effectiveness of TBT-S.

### Aim and objectives

The primary objective of the study is to examine the effectiveness of TBT-S when applied in conjunction with TAU. Specifically, we will measure whether TBT-S in addition to TAU will be more effective than TAU alone in reducing eating disorder psychopathology. We hypothesize that participants receiving TBT-S in addition to TAU will show significantly greater reduction in eating disorder psychopathology from TBT-S pre-assessment to 3-month follow-up, compared to controls.

Our secondary objectives will explore whether participants receiving TBT-S in addition to TAU show reduced clinical impairment, increased quality of life and lower utilization of health care services compared to participants receiving TAU only, at 3-and 12-month follow-ups. Secondary objectives also include the comparison of support experiences in terms of quality of life, psychological wellbeing, carer accommodation and expressed emotional experience of caring for a person with an ED.

## Method

### Study design

We will conduct a non-blinded, randomized, controlled, parallel-group, superiority trial comparing (i) TBT-S plus TAU to (ii) TAU only. Similar control conditions have been used in previous trials of short-term interventions for eating disorders (e.g., Godart et al., 2012; Gowers et al., 2010; Quiles et al., 2025). Four main assessments will be conducted: pre-assessment, post-assessment, and 3- and 12- months follow-up. Eating disorder service utilization during the preceding 3 months will be assessed at pre-assessment and at 3-, 6-, 9-, and 12-months follow-ups. See Figure 1 for Consolidated Standards of Reporting Trials (CONSORT) flow chart (Hopewell et al., 2025) of the trial. The project will be arranged as a multisite study with two collaborating units (Regional department for eating disorders (RASP) at Oslo university hospital and the Department of eating disorders (RAS) at Haukeland university hospital). The collaborating clinics offer TBT-S as part of their standard clinical practice. In accordance with the treatment manual (Hill et al., 2022) there are no requirements regarding the specific time point during the ongoing treatment at which TBT-S should be introduced; clinicians can integrate TBT-S flexibly into ongoing therapy. Thus, the timing of TBT-S within TAU is individualized rather than standardized and depends primarily on practical considerations, including participants’ ability to take time off for the 5-day intervention and the scheduling of TBT-S weeks at the treatment sites (4–6 times per year). Multiple participants are assigned to each TBT-S week before being randomized to receive TBT-S plus TAU or TAU only. Participants randomized to TAU only complete assessments at the same time-points as those randomized to the corresponding TBT-S week, ensuring comparability across study arms.

**Figure 1 fig1:**
[figure not shown]
Consolidated Standards of Reporting Trials (CONSORT) flow chart.

The first author ([name]) is a licensed TBT-S trainer who initiated the intervention in Norway in 2018, conducted the feasibility study in 2023 (Stedal et al., 2023), and is the principal investigator (PI) of the current effectiveness trial. The selected assessment measurements, timeframes, data platforms, recruitment procedures, sample size calculation, and statistical analyses build on the experiences gathered from the feasibility trial. The study has been approved by the Norwegian Regional Committees for Medical and Health Research (REK, 728279), the Data Protection Officer at Oslo University Hospital (PVO, 24/11463) and registered at ClinicalTrials.gov (NCT06497101). Any modifications to the protocol will be reported on clinicaltrials.org, and if relevant, submitted to the Regional committees for Medical and Health Research.

### Participants, eligibility criteria and recruitment

Adults receiving treatment for AN or atypical AN (hereafter AN/AAN as a shorthand to signify that both conditins are being discussed as a singular diagnostic entity) at a local psychiatric center and/or from other qualified treatment provider could be eligible to participate in the study. We will utilize similar recruitment procedures as employed in our TBT-S feasibility study (Stedal et al., 2023). An information pamphlet and website have been designed to facilitate recruitment, complemented by targeted advertisements on social medial platforms. Individuals express interest by sending an e-mail to the TBT-S mailbox ([contact]) hosted by Oslo University Hospital or by filling out an online form which leads to a screening call to determine eligibility.

*Inclusion criteria:* Age ≥18, body mass index (BMI) ≥ 15, currently receiving outpatient treatment for AN/AAN; self-reported medically stable (confined to physical criteria), have a minimum of one support person who can participate in the study.

*Exclusion criteria:* Intellectual developmental disorder or intellectual disability; psychotic disorder or other psychopathology that may affect or prevent participation in the study; diagnosed alcohol or other substance use disorder within 3 months prior to study initiation; ongoing inpatient treatment at the time of study enrollment (participants currently in inpatient care must be discharged and engaged in outpatient treatment before participating in the TBT-S week).

If criteria are fulfilled, informed consent from all study participants, including supports, will be obtained on an encrypted study platform (www.nettskjema.no) requiring identification and two-step authentication.

### Strategies to promote participant retention

During the informed consent process, participants with AN/AAN will be informed that they will receive a gift card upon study completion, and of the possibility to receive TBT-S after the 3-month follow-up if randomized to the control condition. Supports will be informed that they are entered into a lottery to win one of 10 gift cards. To enhance participant retention, small tokens baring the study logo will be sent to participants at two time points: (1) A tote bag upon entering the study and (2) a notebook approximately halfway through the study. At each assessment point, Viedoc will automatically notify participants via e-mail or text message that the questionnaires are available for completion. If participants do not complete the questionnaires, two reminder notifications will be sent prior to the closing of the questionnaire period.

### Randomization and concealment

Included participants will be randomized using Viedoc, an online data collection platform hosted by Oslo University Hospital, Norway, approved by the data protection department at Oslo University Hospital, and monitored by a third party, the Clinical Trials Unit at Oslo University Hospital. This solution is adapted for randomization and gathering participant-reported data via PC, mobile or tablet. The Clinical Trials Unit has generated the randomization sequence in Viedoc which is stratified by treatment location and balanced by being built up of blocks of 2, 4 and 6 occurring in random order. Participant data will be identified by their assigned ID number rather than by name, the Norwegian identifier list will be stored in MedInsight, a Regional committees for Medical and Health Research approved digital participant list solution. All personal data will be stored on encrypted servers, requiring VPN-connection and/or two-step authentication (digital data) in accordance with data management guidelines from regional and local authorities.

Dates for TBT-S treatment weeks will be announced during advertisements so that participants can declare interest and availability for specific treatment weeks in advance of randomization. Allocation to TBT-S treatment groups (specific weeks) is based on the order in which participants declare interest and availability. Due to the nature of the intervention of this study, blinding of participants is impossible. Assessors are also not blinded, but are not included in the delivery of the intervention.

### Interventions

#### Temperament based therapy with support (TBT-S)

Participants in the intervention arm will receive 5 days of TBT-S in addition to ongoing TAU. TBT-S is administered to three to six adults with AN/AAN together with up to four supports each. As described in the TBT-S treatment manual (Hill et al., 2022), the treatment structure consists of five consecutive days of treatment, up to seven h each day. TBT-S is delivered in a multifamily format where both individuals with AN/AAN and supports are included in all the following five treatment strategies: (1) *Neurobiological psychoeducation*. Psychoeducation helps participants recognize how AN could be understood as a biologically influenced illness, emphasizing temperament traits (e.g., anxiety, harm avoidance, altered reward processes) and mechanisms that may be involved in maintaining eating disorder symptoms; (2) *Experiential learning activities addressing eating disorder neurobiology and traits*. The experiential activities are developed to aid participants experience how traits such as cognitive inflexibility can be experienced, how to maneuver toward recovery and how supports can be of help and, importantly, they help provide insight through action rather than discussion alone; (3) *Client and support skills training*. The skills training aspect of TBT-S teaches practical, trait-aligned tools to respond more effectively to eating disorder behaviors and to ensure consistent use of skills for recovery in daily life; (4) *Meal coaching*. Participants practice skills in real time together with supports and clinicians to help tolerate distress, reduce rituals and reinforce adaptive behaviors pre, post and during meals; (5) *TBT-S behavioral agreement*. The behavioral agreement is an individually tailored written plan, developed collaboratively by the participant with AN/AAN, their supports and the clinical team. It clearly outlines recovery-related behaviors and the role of supports. The agreement should help with accountability and provides a structure to facilitate consistent implementation of treatment strategies (Hill et al., 2022). Drop-out rates will be tracked systematically. We have previously translated and adapted the TBT-S material to Norwegian and assessed its feasibility and acceptability with Norwegian participants (Stedal et al., 2023).

#### Treatment as usual (TAU)

All participants will continue the treatment they receive when entering the study. TAU is defined as any treatment the participants receive for their AN/AAN other than TBT-S. Thus, TAU will vary and could include a combination of both psychotherapy and pharmacologic treatments. Participants in the control condition will differ from participants in the treatment condition in that they will not receive TBT-S in addition to TAU. In line with the recommendations by Petersson et al. (2023), we will give a detailed description of TAU, including a description of the content, and referring to clinical guidelines. At pre-assessment, and at 3-, 6-, 9- and 12 months follow-up assessments, participants will answer a questionnaire about the treatment they have received for their eating disorder in the last 3 months. The questionnaire includes items about level of treatment (e.g., outpatient psychiatric, inpatient psychiatric, general practitioner, and private vs. public), type of treatment (e.g., individual therapy, group therapy), intensity of treatment (e.g., number for days, sessions), and about whether and what pharmacological treatment the patient has used.

### Therapist competence and adherence

The two collaborating eating disorder clinics have a team of trained TBT-S clinicians. The TBT-S therapist trainings are structured in a three-tier manner, outlined on https://tbtstraining.com/training-levels/. The PI will provide training of untrained staff, as well as supervision of both clinics throughout the project period. At each site, TBT-S treatment weeks will be rated for intervention fidelity and therapeutic competence using checklists developed specifically for the study. Supervision based on these ratings will be provided to the clinicians if needed. Staff requirements for TBT-S are three clinicians, one dietician and one medical staff (Hill et al., 2022).

### Safety monitoring and adverse events

In cases where suicidal ideation is reported during the pre-assessment interviews, the interviewer will advise the patient to promptly consult their current eating disorder therapist or treatment provider. When participants register adverse events—defined as admittance to a somatic care unit or a psychiatric intensive care unit—in Viedoc, they will be prompted to provide additional information. At the same time, an automatic notification will be sent to the PI. These responses will be assessed by the project group every 6 months, and reviewed as to whether or not the incident could be caused by participating in the study. This assessment will be scored as: Unlikely, Somewhat Likely, Likely, Very Likely.

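### The adverse event definition and its self-registration route leave out non-intensive psychiatric admissions, suicide attempts without a qualifying admission, and deaths

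*Protocol article*

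**What the plan says.** Under Safety monitoring and adverse events, the protocol article gives a closed definition: an adverse event is "defined as admittance to a somatic care unit or a psychiatric intensive care unit". Any somatic admission counts. On the psychiatric side, only intensive care does.

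The same section describes one reporting route, which begins "When participants register adverse events" in Viedoc. The entry triggers a request for more information and an automatic notice to the principal investigator. On review it says: "These responses will be assessed by the project group every 6 months". The project group then scores on a four-level scale how likely it is that study participation caused the event. Suicidality is handled at one time point ("In cases where suicidal ideation is reported during the pre-assessment interviews"), by advising the participant to contact their own treatment provider.

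A separate stream appears under Treatment as usual (TAU). The article states: "At pre-assessment, and at 3-, 6-, 9- and 12 months follow-up assessments, participants will answer a questionnaire about the treatment they have received". That form covers "level of treatment (e.g., outpatient psychiatric, inpatient psychiatric, general practitioner, and private vs. public", with a three-month look-back. Table 1 lists it as the health services form at pre-assessment and at 3, 6, 9 and 12 months. The Measurements section uses it to describe TAU and to assess cost-effectiveness. No text connects it to the adverse event review.

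**The concern.** The illness is one in which the excluded events are to be expected. The Introduction reports raised mortality and says that chronic courses "typically involve severe long-term consequences with several admissions and readmissions to hospital". Participants must be in outpatient treatment and not inpatients at enrolment, so an unplanned admission during follow-up is a visible sign of deterioration. If the safety process works only from the stated definition and route, a participant admitted to an ordinary psychiatric or eating disorder ward is never assessed for relatedness to the trial, even though the trial may hold the admission on another form. A death has no stated way into the process at all.

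An analysis plan cannot repair this later. It can tabulate only what was defined and collected as an adverse event.

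**Working it through.** No arithmetic applies: the article states no admission rate, safety test or event count. The check sets each event type against the definition and route (Safety monitoring and adverse events) and against the other data streams (Treatment as usual, Measurements, Table 1).

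| Event | Meets the definition? | Stated route to the review? | Held elsewhere? |
|---|---|---|---|
| Somatic admission, any unit | Yes | Yes, self-registered | Possibly, as service use |
| Psychiatric intensive care admission | Yes | Yes, self-registered | Possibly, as service use |
| Non-intensive psychiatric or psychiatric eating disorder ward admission | No | None | Yes, if for the eating disorder: service form at 3, 6, 9 and 12 months |
| Suicide attempt or self-harm leading to a somatic or psychiatric intensive care admission | Yes, as that admission | Yes, self-registered | Possibly |
| Suicide attempt or self-harm without such an admission | No | None | No dedicated item described |
| Death | No | None, and the participant cannot register it | None described |

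Three details bear on how far the service form closes the gap.

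1. **Scope.** It asks about treatment for the eating disorder. A psychiatric admission for another reason, such as a suicidal crisis, may not appear on it. The broader TIC-P is given only at pre-assessment, 3 and 12 months (Table 1).
2. **Source.** Like the Viedoc entry, it is self-report, so it captures neither deaths nor participants who stop responding.
3. **Destination.** Only the participants' adverse event entries go to the project group. Inpatient answers on the service form trigger no alert and no relatedness score.

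After pre-assessment, Table 1 schedules no clinical interview, so no later clinician contact is described that would pick up a suicide attempt.

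**The case against.** The strongest reply is that ordinary psychiatric admissions are not lost. Inpatient treatment for the eating disorder is reported in both arms at 3, 6, 9 and 12 months, and health care utilisation is a declared secondary outcome, compared between arms at 3 and 12 months. This stands in part: the trial can see an imbalance in such admissions. What is missing is their recognition and review as possible harms, and the service form does not reach the other two kinds of event.

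Second, TAU includes any treatment for the illness other than TBT-S, and inpatient psychiatric care is one of its listed levels. A planned eating disorder admission may therefore be part of care and not a harm. This also stands, and it is why the fix refers to unplanned admissions.

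Third, the article is condensed, and the full protocol may handle deaths and site-reported events. That is possible. But the article does not leave the definition open: it states one, and deaths are not in it. The wording on self-registration does not expressly exclude other routes. It simply describes no other.

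Three stronger readings are tempting and should not be drawn.

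- A reader might infer that the plan will produce a misleading safety comparison between arms. The article promises no such comparison and no adverse event table by arm. It describes case-by-case causality scoring, and a tabulation may be left to the analysis plan.
- A reader might infer that all suicide attempts are excluded. Those leading to a qualifying admission are counted.
- A reader might infer that self-registration combined with drop-out in TAU would hide harm from TBT-S. The Discussion says only that allocation to TAU could be discouraging and so raise the risk of drop-out. If TAU events were under-registered as a result, TBT-S would look worse by comparison, not better. No direction of bias can be claimed.

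**Conclusion.** The point holds as a badly fixed rule for recording and reviewing adverse events. Followed as written, the plan sends three kinds of event to no review: non-intensive psychiatric or eating disorder ward admissions, suicide attempts or self-harm without a qualifying admission, and deaths. The first is partly observed as service use; for the other two no route is described.

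The size cannot be put in numbers. The article gives no admission, self-harm or death rate for this population, and any count would rest on assumed rates. The conclusion does not depend on one.

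It rests on two assumptions: that the definition is meant as exhaustive, as its wording suggests, and that no further reporting route exists in a document not shown. The primary endpoint, its analysis and the sample size are unaffected. The change is worth making because it improves safety ascertainment at low cost.

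**What to change.** Reconcile the adverse event section with the TAU section as follows.

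1. Define recorded events as any unplanned hospital admission (somatic, psychiatric or eating disorder unit, at any level of care), any suicide attempt or self-harm needing care, and death.
2. Send inpatient answers on the existing service form at 3, 6, 9 and 12 months to the same relatedness review, where planned admissions can be told apart from unplanned ones.
3. Name a source other than the participant for deaths and serious events: site staff or the enrolled support. Every participant has at least one support in the study.
4. Report events by randomised arm, separately for 0–3 months and after 3 months, because TAU participants may opt to receive TBT-S after the 3-month assessment.

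The cost is a protocol amendment, a small change in Viedoc and more events for the project group to review. Because 31 participants had been randomised when the article was submitted, there will be two ascertainment periods. Applying the service-form answers retrospectively to those participants offsets this in part, for inpatient eating disorder treatment only. At that point 120 − 31 = 89 of the planned participants were still to be randomised, and inclusion is expected to run to December 2027, so an early amendment would cover most of the trial.
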